This confirmatory efficacy R01 trial focuses on two non-pharmacological treatments that each work for some SAD patients: light therapy (LT; i.e., daily exposure to bright artificial light during the symptomatic months), and SAD-tailored group cognitive-behavioral therapy (CBT-SAD) [11]. Substantial evidence supports LT as an efficacious acute SAD treatment [12]. In our previously completed R01-level efficacy trial enrolling 177 adults with SAD, CBT-SAD and LT were very similar in terms of symptom improvement and the proportions in remission at post-treatment (47.6% CBT-SAD, 47.2% LT) [13]. However, two winters later, CBT-SAD was associated with significantly fewer depression recurrences (27.3% CBT-SAD, 45.6% LT) and lower depression severity than LT [14]. These findings suggest that slightly more than one-quarter of those treated with CBT-SAD and slightly less than half of those treated with LT have a depression recurrence, highlighting the need for reliable strategies for precision medicine in clinical practice. In the current project, we apply the experimental therapeutics approach to determine how each treatment works and to identify the best candidates for each. Consistent with the NIMH’s focus on biological endpoints, we will ascertain whether theoretically derived candidate biomarkers of each treatment’s target and effect are prescriptive of better outcomes in that treatment vs. the other.

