### Objectives {7}

Our goal is to inform evidence-based guidelines for personalized medicine using CBT-SAD and LT, specifically for determining [1] which patients are best suited for which type(s) of treatment in terms of recurrence prevention, and [2] whether the selected treatment engages its intended target. We will ascertain whether theoretically derived candidate biomarkers of each treatment’s target and effect are prescriptive of better outcomes in that treatment vs. the other. We will examine the established chronobiological biomarker of LT’s target and effect, PAD, and explore the PIPR as a candidate biomarker of melanopsin-driven retinal subsensitivity with specificity to LT. We will use self-reported seasonal beliefs as the established target and mechanism of CBT-SAD and also map this construct onto theoretically relevant biomarkers of reduced emotional reactivity to seasonal stimuli, pupil dilation and sustained frontal gamma band EEG responses to seasonal words. In addition to determining whether these interventions engage associated change mechanisms, we will test the efficacy of a “switch” decision rule upon recurrence the next winter to inform clinical decision-making for managing SAD recurrences following a first-line treatment.

In this confirmatory efficacy R01, adults with SAD (target *N* = 160) will be randomized to two equal-probability 6-week treatment conditions in winter 1: CBT-SAD or LT. We will follow subjects in winter 2 and if a depression recurrence occurs, we will cross them over into the alternate treatment (i.e., switch to CBT-SAD upon recurrence after LT, switch to LT upon recurrence after CBT-SAD). All subjects will be assessed at follow-up in winter 3. Biomarker assessments will occur at pre-, mid-, and post-treatment in winter 1; at winter 2 follow-up (and again at mid- and post-treatment for those with depression recurrences crossed-over into the other treatment); and at winter 3 follow-up. This work will yield longitudinal data on targets, their engagement, and stability, thereby increasing the impact of future dissemination efforts.

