### Trial design {8}

This is a head-to-head confirmatory efficacy trial comparing CBT-SAD and LT (with equal-probability allocation) designed to test superiority of one treatment over the other in depression recurrences at winter 2 follow-up. Participants with recurrences at winter 2 follow-up will be offered the opportunity to cross-over into the alternate treatment. All participants are followed-up at winter 3 (Fig. 1).

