### Sample size {14}

With a target *N* = 160 (80 subjects in each of the two treatments), the study will have 80% power to detect main effect differences of 22% (e.g., 28% vs. 50%) in winter 2 recurrence, which we expect at a naturalistic follow-up [14, 44]. Sample sizes for comparisons of winter 3 recurrence will depend on the number of recurrences at winter 2. Based on the recurrence rates observed in our prior study, we project that there will be about 37 recurrences in the LT group and 22 recurrences in the CBT-SAD group. This will provide 80% power to detect a difference in winter 3 recurrence of 35% (e.g., 60% vs. 25%) between CBT-SAD➔LT and LT➔CBT-SAD and a difference of 27% (e.g., 23% vs. 50%) between CBT-SAD and LT subjects without winter 2 recurrence. For biomarker comparisons, there will be 80% power to detect differences of 0.45 standard deviation (SD) in post-treatment values or in pre-post treatment changes between CBT-SAD and LT. Power for detecting relationships between biomarkers and outcomes were based on the odds ratio associated with an increase of 1 SD in the biomarker value or its change. For post-treatment remission, there will be 80% power to detect an OR of 2.2 in the CBT-SAD or LT group and a 2.4-fold difference in the ORs for the two treatments. For winter 2 recurrence, there will be 80% power to detect an OR of 2.2 in the LT group, an OR of 2.8 in the CBT-SAD group, and a 2.9-fold difference in their ORs. There was minimal attrition (4.5%) in our previous study, and we anticipate similar retention in this study. However, with attrition as high as 20%, there will be 80% power to detect a difference in winter 2 recurrence of 24% between CBT-SAD and LT and a difference of 39% in winter 3 recurrence between the two switch groups. Empirical sample size estimates^21^ indicate that the study will have at least 80% power to detect a mediated effect if the regression coefficient for the direct effect of treatment after adjustment for the mediator is at least .39 and the coefficients for the effect of treatment on the mediator and the effect of the mediator on outcome after adjustment for treatment are at least .26.

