We will test mediating effects of candidate biomarkers on change in depressive symptoms using parallel process latent growth curve modeling (LGCM) [72–74]. These tests will focus on treatment outcomes through winter 2 and winter 3 follow-up to elucidate the mechanisms underlying the long-term benefit of CBT-SAD. Analyses will include all available information from multiple biomarker assessments and multiple assessments of depressive symptoms (on the SIGH-SAD and BDI-II), modeling latent intercept and linear slope factors for individual biomarkers and symptoms. Each biomarker will be analyzed in a separate model to avoid undue model complexity. Parallel process LGCM allows for estimation of indirect effect magnitude from treatment assignment, through change in biomarker, to change in depressive symptoms, as well as the direct effect from treatment to change in symptoms. We will calculate established mediation effect size indices from these models such as proportion of total possible effect mediated [75]. LGCM will be conducted using full-information maximum likelihood estimation in Mplus [76].

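### Aim 4's linear slopes through winter 3 do not isolate biomarker change during treatment, and the model has no stated handling of the winter 2 switch

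*Protocol article*

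**What the plan says.** The protocol article, Statistical methods {20a}, Aim 4, specifies parallel process latent growth curve models, one biomarker at a time, "modeling latent intercept and linear slope factors for individual biomarkers and symptoms". All available biomarker and symptom assessments enter. The span is stated as follows: "These tests will focus on treatment outcomes through winter 2 and winter 3 follow-up to elucidate the mechanisms". The indirect effect runs from assigned treatment through biomarker change to symptom change. No piecewise or freely estimated time loading is named, the time scores are not given, and nothing is said about participants who switch.

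On the switch, Objectives {7} says that "if a depression recurrence occurs, we will cross them over into the alternate treatment", while Trial design {8} says "Participants with recurrences at winter 2 follow-up will be offered the opportunity to cross-over into the alternate treatment". Sample size {14} assumes "80 subjects in each of the two treatments" and states: "we project that there will be about 37 recurrences in the LT group and 22 recurrences in the CBT-SAD group".

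Other aims do deal with the switch. Aim 1 limits its winter 3 comparison to those free of recurrence at winter 2, and Aim 3 lets treatment vary over time in its longitudinal model.

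**The concern.** The Background says that change in seasonal beliefs over the course of treatment mediates both acute improvement and lower depression one and two winters later. Testing that needs a mediator measured over the treatment weeks and an outcome measured afterwards. One slope for the biomarker and one for symptoms, both over the same two years, supplies neither. Each slope mixes the acute fall with the course over later winters, and neither precedes the other.

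By winter 3, a sizeable and unequal share of each arm may also have received the other treatment, and the trigger for the switch is the depression outcome itself. Original assignment then no longer identifies the treatment whose mechanism is being estimated. Aim 4 is one of four specific aims, and the trial's formal estimate of an indirect effect rests on it.

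**Working it through.** **1. Projected switchers.** Inputs: 80 per arm (Sample size {14}) and prior recurrence of "27.3% CBT-SAD, 45.6% LT" (Background {6a}).

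- LT: 80 × 0.456 = 36.5, about 37. CBT-SAD: 80 × 0.273 = 21.8, about 22. The plan's projection reproduces.
- Eligible to switch: (37 + 22)/160 = 59/160 = 36.9%. By arm: 37/80 = 46% and 22/80 = 28%.
- Uptake is not stated. At 90%, 75% and 50% uptake the share is 33.2%, 27.7% and 18.4%. At full uptake with 4.5% or 20% attrition it is about 35% or 29.5%.

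**2. What a single linear slope weighs.** With complete data and equal residual variances (assumed), the mean slope is the least-squares slope. The weight of the visit at time t is (t − mean)/SS, where SS is the sum of squared deviations. Follow-ups in January of the next two winters are taken as weeks 52 and 104 (an approximation).

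Five waves, weeks 0, 3, 6, 52, 104: mean 33; SS = 1089 + 900 + 729 + 361 + 5041 = 8120.

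| Week | 0 | 3 | 6 | 52 | 104 |
|---|---|---|---|---|---|
| Calendar weight | -.0041 | -.0037 | -.0033 | +.0023 | +.0087 |
| Equally spaced weight | -.2 | -.1 | 0 | +.1 | +.2 |

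- Ending at winter 2 (weeks 0, 3, 6, 52; mean 15.25, SS 1818.75), the week 6 weight is -9.25/1818.75 = -.0051.
- PAD has no mid-treatment value (weeks 0, 6, 52, 104; mean 40.5, SS 6995). Its post-treatment weight is -34.5/6995 = -.0049, or -.1 with equal spacing.

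**3. Consequence, with assumed SIGH-SAD means.** The article reports no mean trajectories, so all scores here are illustrative. Baseline is 28 and both follow-ups are 20.

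| Acute course | 5 waves, calendar | 9 occasions, calendar | 9 occasions, equally spaced |
|---|---|---|---|
| Strong (post-treatment 10) | +0.04/year | +0.17/year | -1.28/wave |
| Weak (post-treatment 20) | -2.5/year | -2.6/year | -1.09/wave |

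The five-wave scores are 28, 20, 10, 20, 20 and 28, 24, 20, 20, 20. For example, the strong course gives (-924 - 600 - 270 + 380 + 1420)/8120 = 6/8120 per week. The nine occasions follow the actual SIGH-SAD schedule (pre-treatment, weeks 1–5, post-treatment, two winters) with a linear fall. In calendar time the weaker responder has the more favourable slope. With nine equally spaced occasions the ordering is right, because the post-treatment weight is then +2/60 = +.033.

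**4. Does the whole slope change sign?** Assume pre-treatment 28, post-treatment 12, and equal winter 2 and winter 3 means. In calendar time the slope turns positive only if the follow-up mean exceeds 17.7 to 20.6, depending on the shape of the acute fall. That means 36–54% of the 16-point drop is regained. With equally spaced waves, 73–117% must be regained. A sustained response (28, 20, 10, 10, 10) gives -894/8120 × 52 = -5.7/year, which is the right sign.

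**5. Size.** For pre-treatment 28, post-treatment 10–14 and follow-up 10–24, the calendar-time slope is at most about 0.11 point per week in absolute value. The acute change is 2.3 to 3.0 points per week. The slope does not measure the acute change in any of these cases, whatever its sign.

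**The case against.** The strongest reply has four parts.

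- **The article is condensed.** Piecewise models also use linear slope factors. The text does not say that a single slope spans the whole trial or that winters 2 and 3 share a model, and time scores and knots may be in an analysis plan that is not shown. This stands as a limit on certainty: a single slope is the natural reading, not a stated fact. But the text does fix a linear form, all assessments, a span to winter 3 and original assignment as exposure. On a calendar scale, ending at winter 2 does not remove the negative post-treatment weight.
- **Aim 2 already relates pre-post biomarker change to winter 2 outcomes.** True, and this covers part of the question. Aim 2 estimates no indirect effect, which is what Aim 4 is for.
- **Analysis by assignment follows the intent-to-treat principle.** That defends an effect of assignment on winter 3 outcome. It does not make assignment identify one treatment's mechanism after a switch triggered by outcome.
- **Missing temporal order is a known limitation of parallel process models.** Agreed, but here the hypothesis is explicitly ordered in time, and the visit schedule allows an ordered model.

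A reader might infer that the model gives acute change the wrong sign. The documents do not support that: the result depends on unstated time coding and unreported means, and under many plausible values the slope stays negative. A reader might also infer that 37% will have received the other treatment. Since Trial design {8} describes an offer, 37% is the share projected to be eligible.

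**Conclusion.** The concern holds in limited form. As written, Aim 4's linear slope does not measure biomarker change during treatment and gives no order between mediator and outcome. On a calendar scale it weights post-treatment values negatively (-.0033 per week for five waves through winter 3, -.0051 for four waves ending at winter 2), so the indirect effect can be distorted. Reversal of its sign is possible but not shown.

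Winter 3 data, and possibly the mid- and post-treatment values from winter 2 re-treatment, from up to 59/160 participants stay under the original arm with no stated handling. The projected imbalance is 46% against 28%.

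This rests on reading the text as one slope per process, on follow-up at about weeks 52 and 104, on equal residual variances, and on full uptake and retention for the 37%. The winter 2 follow-up itself comes before any switch and is not contaminated. Aim 1 is untouched, so the primary conclusion does not depend on this. The point matters for the mechanistic claim.

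**What to change.** Respecify the main Aim 4 mediation test as a piecewise or latent-change model. The mediator is change from pre- to post-treatment; for PAD, which has only those two values in winter 1, use a latent change score. The outcome is the winter 2 depression score, taken before any switch and regressed on mediator change, treatment and baseline. State the time scores.

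Label winter 3 mediation exploratory. Say how post-switch data enter: modelled separately, or with treatment allowed to vary over time as in Aim 3. Say whether winter 2 re-treatment assessments are used. Reconcile the Objectives and Trial design wording on whether the switch is made or offered, and report uptake by arm.

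The cost is a few more parameters per model and a respecification in Mplus. No new data are needed. The test leans more on post-treatment biomarkers, some of which may be missing: 26 participants were in treatment in March 2020, and the Discussion says in-lab biomarker sessions were halted. The full-information estimation already planned can accommodate this under its usual missing-at-random assumption.

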To examine mechanistic differences between CBT-SAD and LT, mixed effects linear regression with subject as a random effect will be used to model biomarker changes during treatment as a function of time, treatment, and their interaction. We will also model the relationship between biomarker change and change depressive symptoms as a function of treatment by letting the regression coefficient differ between CBT-SAD and LT. This will provide a test of whether potential mediators of effect are treatment-specific. The predictive value of biomarkers at baseline, their pre-post treatment change, and the persistence of the change at follow-up will be examined using logistic regression (for post-treatment remission and winter 2 recurrence) and linear regression (for SIGH-SAD and BDI-II scores) with post-treatment and winter 2 outcomes as dependent variables. Interactions between the biomarkers and treatment will be used to test if the associations with outcomes differ in the CBT-SAD and LT groups. Adherence will be included in ancillary analyses to test its effect on the relationships of treatment with biomarkers and LT or CBT-SAD outcomes. The relationships between biomarkers and outcomes will be validated by examining how well they predict post-treatment and winter 3 outcomes for subjects who experience a recurrence at winter 2 and are switched to the alternative treatment. Data from the cross-over subjects will also be analyzed using mixed linear regression to compare within-person differences in pre-treatment biomarkers and their changes during their initial and subsequent treatments. Treatment, time point (winter 1 or 2), and their interaction will be included to test the effect of treatment sequence on within-person differences in biomarker responses to CBT-SAD and LT.

##### Aim 3

Logistic and linear regressions similar to those for Aim 1 will be used to compare the effect of switching from CBT-SAD➔LT versus LT➔CBT-SAD on winter 3 recurrence and depression scores. Post hoc adjustment for any differences between switch groups in baseline characteristics, treatment response, and biomarker profiles will be done by including them as covariates. Mixed linear regression will be used to longitudinally model depression scores over the three winters, with treatment as a time-varying covariate.

##### Aim 4

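### Aim 4 describes one biomarker-to-symptom path for both arms, although the protocol treats that path as possibly arm-specific; arm-specific indirect effects should be reported beside the pooled one

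*Protocol article*

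**What the plan says.** All statements are in the protocol article.

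- **Statistical methods {20a}, Aim 4.** Treatment assignment is the exposure, and each biomarker has its own model: "Parallel process LGCM allows for estimation of indirect effect magnitude from treatment assignment, through change in biomarker, to change in depressive symptoms". A direct effect of treatment on symptom change is estimated alongside, and mediation effect-size indices are calculated from these models. The focus is winters 2 and 3 and the mechanism of CBT-SAD's long-term benefit. No treatment-by-biomarker term and no two-group model is mentioned.
- **Sample size {14}.** With "80 subjects in each of the two treatments", the study is said to have "at least 80% power to detect a mediated effect" provided that "the regression coefficient for the direct effect of treatment after adjustment for the mediator is at least .39" and that the coefficients for treatment on mediator and for "the effect of the mediator on outcome after adjustment for treatment are at least .26". There is one mediator-to-outcome coefficient, not one per arm.
- **Statistical methods {20a}, Aim 2.** Biomarker change is related to symptom change by "letting the regression coefficient differ between CBT-SAD and LT", as a test of treatment specificity. Biomarker-by-treatment interactions are also planned for post-treatment and winter 2 outcomes.
- **Outcomes {12}, Table 1.** Candidate mediators are marked as belonging either to LT (PAD, PIPR, CSM) or to CBT-SAD (word-response pupil and EEG measures, SBQ, DAS, BADS).
- **Sample size {14}, biomarker associations.** For remission, the plan gives the detectable contrast between arms as "a 2.4-fold difference in the ORs for the two treatments"; for winter 2 recurrence it gives 2.9-fold.

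**The concern.** Splitting a treatment effect into one indirect and one direct part is unambiguous when the mediator relates to the outcome equally in both arms. Once that path differs, there are two indirect effects, one for each arm's path, and a one-path model returns a blend of them.

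Aim 4 is meant to explain why CBT-SAD lasts longer than LT. A blended figure could be read as CBT-SAD's mechanism when part of it reflects how the marker behaves under LT. For a marker that works only in CBT-SAD, the mediated effect would look weaker and the direct effect larger than they are under the CBT-SAD path. For a marker that works mainly in LT, the error for CBT-SAD runs the other way. Aim 2 raises the question of arm-specific paths, but nothing in the text carries its answer into the Aim 4 decomposition.

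**Working it through.** **Inputs.** From Sample size {14}: 80 per arm, a = .26 (treatment to mediator), b = .26 (mediator to outcome), c′ = .39 (direct). Not given in the document and assumed here: two-sided alpha of 0.05, standardised coefficients, unit residual variances and, for the growth model, five equally spaced waves with linear slopes.

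**1. The plan's own figure.** Simulating a single-mediator model at N = 160 with treatment coded ±1 and one common b, and requiring both a and b to be significant, gives about 81% power. The stated 80% reproduces, but the calculation has only one path. (A Sobel test would give about 64%, so the joint test appears to be the basis.)

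**2. What a one-path model estimates.** With n₁, n₀ subjects and within-arm biomarker-slope variances v₁, v₀:

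b_pooled = (n₁v₁b_CBT + n₀v₀b_LT) / (n₁v₁ + n₀v₀)

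With equal n and equal v this is the simple mean of the two paths.

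**3. Decomposition.** On a 0/1 treatment scale, a = 2 × .26 = .52 and c′ = 2 × .39 = .78. A single-group parallel-process growth model, fitted by maximum likelihood to population moments, gave the one-path values below.

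| True b (CBT-SAD, LT) | One-path indirect | One-path direct | Indirect under CBT-SAD path | Indirect under LT path | One-path ÷ CBT-SAD |
|---|---|---|---|---|---|
| .26, .26 | .135 | .780 | .135 | .135 | 100% |
| .26, 0 | .068 | .848 | .135 | 0 | 50% |
| .26, .13 | .101 | .814 | .135 | .068 | 75% |
| .13, .26 | .101 | .746 | .068 | .135 | 150% |

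Second row by hand: b_pooled = (.26 + 0)/2 = .13, and .52 × .13 = .068. The total effect is .780 + .52 × .26 = .915, so the direct part is .915 − .068 = .848 after rounding. Under the CBT-SAD path the split is .135 and .780; under the LT path it is 0 and .915. The one-path result lies midway between them.

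**4. Unequal slope variances.** With b = .26 and 0 and v in the ratio 2:1 (CBT-SAD:LT), b_pooled = 2 × .26/3 = .173, which is 67% of the CBT-SAD path. With 1:2 it is .26/3 = .087, or 33%.

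**5. Power at N = 160 (joint test).**

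| True b (CBT-SAD, LT) | Pooled path | CBT-SAD-specific path |
|---|---|---|
| .26, .26 | about 81% | about 56% |
| .26, 0 | about 33% | about 56% |

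The fall from 81% to 56% reflects that only 80 participants inform a CBT-SAD path. The further fall from 56% to 33% is due to pooling with an arm in which the path is absent. With .26 and .13 the pooled test still does somewhat better (about 62% against 55%).

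**The case against.** **The common path is inferred.** Aim 4 does not say that the path is held equal across arms, and the quoted sentence describes what the method allows. A condensed article may leave such detail to an analysis plan that is not shown. This stands as a limit. The inference rests on assignment as the exposure, one indirect and one direct effect, and a power statement with one coefficient. A reader might go further and take it that the plan imposes equality; the text does not state that.

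**A pooled indirect effect is a legitimate average.** This stands. A reader might infer that mediation is generally understated, or that a full mediator would always look partial. Neither follows: there is no bias with equal paths, the arm with the weaker path is overstated, and the size of the mediated effect depends on which arm's path is used.

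**Arm differences are already examined in Aim 2.** This stands in part. Those interactions would flag a difference for change during treatment and for post-treatment and winter 2 outcomes. They do not supply the indirect and direct effects through winter 3, and no link to Aim 4 is stated.

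**The document does not assert a difference.** Aim 2 is a test, and the 2.4- and 2.9-fold figures are minimum detectable differences in odds ratios, not expected differences in slope-to-slope paths. For seasonal beliefs, the background also describes specificity as greater change in CBT-SAD, which a one-path model captures. It is therefore fair to call arm-specific paths a working hypothesis, and no more.

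**Arm-specific paths are costly.** This stands. One might suppose that freeing the path is nearly free, but at the planning values with equal paths the test falls from about 81% to about 56%. That argues against replacing the pooled effect.

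**Conclusion.** The tension is real but conditional. As written, Aim 4 and its power statement describe a single path, while Table 1 and Aim 2 keep open that the path belongs to one arm. If it does, the pooled indirect effect is a weighted average and should not be read as CBT-SAD's mechanism. In the illustrative case of a path present only in CBT-SAD, it is about 50% of that arm's indirect effect (33% to 67% for slope-variance ratios of 1:2 to 2:1), and power is about 33% in place of the planned 80%. If the paths are equal, the planned analysis is unbiased and more powerful.

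The figures rest on the assumptions listed with the inputs, and on no unmeasured confounding of mediator and outcome. The power figures come from a single-mediator regression, not from the latent growth model itself. The point concerns a mechanistic aim; the primary comparison of winter 2 recurrence is unaffected. It is worth correcting because explaining CBT-SAD's durability is the stated purpose of Aim 4.

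**What to change.** 1. Keep the common-path indirect effect as planned.
2. Add to each Aim 4 model a treatment × biomarker-slope term, or fit a two-group growth model in which only the slope-to-slope path is freed (besides the slope means that carry the treatment effect).
3. Next to the pooled results, report the indirect and direct effects under the CBT-SAD path and under the LT path, with intervals.
4. State that when the paths differ, the pooled proportion mediated will not be interpreted as CBT-SAD's mechanism.
5. State in Sample size {14} that the 80% mediation power assumes a path common to both arms.

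The cost is one extra parameter per model and a few sentences; no new data are needed. The downside is lower precision of the arm-specific estimates (about 56% power against about 81% for the pooled test at the planning values with equal paths), which is why the pooled effect should stay. If the full analysis plan already frees the path by arm, saying so in Aim 4, together with item 5, would be enough.
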